### Quality control

The protocol will be reviewed and revised by experts in acupuncture, rheumatology, orthopaedics, methodology and statistics. A pre-specified standard operating procedure (which includes screening patients, taking X-rays, acupuncture, filling out the eCRF, assessing outcomes and data management) will be used. Online monitoring and on-site monitoring will be adopted in this trial. All modifications of the data can be traced through the eCRF.

### Sample size

Acupuncture is a complex intervention that is different from drugs. If the acupoints in the study were changed, then the efficacy of the acupuncture would be altered. For this reason, we do not use data from the literature to calculate the sample size. Based on previous pilot trials [33] and clinical experience, the success rates of the EA, MA and SA groups are expected to be 70%, 60% and 40%, respectively. A two-sided significance level of 0.025 will avoid the inflation of type I errors. A sample size of 56 patients in each group is estimated to have 80% power to detect significant differences between the EA group and the SA group. A sample size of 128 patients in each group is estimated to have 80% power to detect significant differences between the MA group and the SA group. To compensate for a 20% loss to follow-up, the sample size was increased to 160 patients in each group.

### Statistical analysis

Patients’ baseline characteristics will be summarised by treatment arm. Continuous variables will be described using the mean (standard deviation), or the median (interquartile range) if the normality assumption is violated. One-way analysis of variance (ANOVA) or Kruskal–Wallis one-way ANOVA (if normality is violated) will be used for comparison among the three groups. Categorical variables will be described using the frequency (percentage) and compared using the chi-squared test. All analyses will be performed using SAS 9.3 (Cary, NC).

All efficacy analyses will be performed using the intention-to-treat set, which will consist of all patients who have been randomised and have finished at least one post-baseline measurement. For the primary comparisons, we will calculate the success rates at 8 weeks and compare the EA group and the SA group (and between the MA group and the SA group) using the *Z*-test for proportions. We set α = 0.025 to adjust for the multiple comparison.

For the secondary outcomes, continuous variables with repeated measurement, including WOMAC pain, function and stiffness scores, NRS and quality of life (SF-12), will be compared among the three groups at all follow-up time points using a mixed-effect model with repeated measurement methods. If there is a normality violation in the continuous variables, a transformation will be performed before the test. The adverse event rate will be summarised by group and compared using a chi-squared test (or Fisher’s exact test).

A generalised linear mixed-effect model will be used in the sensitivity analysis. This will be performed using the per-protocol set, which includes only those who complete ≥20 sessions and have no major protocol violations (taking other drugs during the trial, etc.). We will perform a subgroup analysis according to the Kellgren–Lawrence grade.

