#### Randomisation and allocation concealment

Eligible patients will be randomly assigned to the EA group, MA group or SA group in a 1:1:1 ratio using a central web-based randomisation tool. The blocked randomisation sequence will be generated with the software SAS 9.3 (SAS Institute, Cary, NC, USA) by an independent statistician ([name], State Key Laboratory of Translational Cardiovascular Medicine, China), who is not involved in the implementation or statistical analysis of the trial. Randomisation will be stratified within the nine enrolment hospitals with a random block size of 6 or 9. The sequence will be embedded into the software (Beijing Guide Technology Co, Ltd). The clinical research coordinator will input the patient information on a tablet computer and will be given a random number.

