#### Primary outcome

The primary outcome will be the success rate [25]: the proportion of patients achieving a minimal clinically important improvement (MCII) [13, 26], which is defined as ≥2 points on the NRS and ≥6 points in the Western Ontario and McMaster Universities Osteoarthritis Index (WOMAC) function score at week 8 compared with baseline.

The primary outcome encompasses valid and reliable pain [27] and function [28] measures for KOA. Average knee pain in the previous week will be assessed using an 11-point NRS ranging from ‘no pain’ (0) to ‘worst pain’ (10) (MCII = 2 units, which is extrapolated from 19.9-mm MCII reported for 100-mm visual analogue scales [26, 29]). Physical function will be assessed using the WOMAC function subscale (Likert version 3.1), scored from 0 to 68 with lower scores indicating better function (MCII = 6 units, which is extrapolated from 9.1-unit MCII reported for standardised 100-unit WOMAC function subscale [26]).

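### The primary Z-test leaves out the hospital strata and the baseline NRS and WOMAC function scores; accounting for them would be a free gain in precision, mainly for MA versus SA

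*Protocol article*

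**What the plan says.** **Primary test.** The Statistical analysis section compares week-8 success between EA and SA "and between the MA group and the SA group) using the *Z*-test for proportions", each comparison at 0.025. It names no stratification and no covariate.

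**Randomisation.** The Randomisation and allocation concealment section states: "Randomisation will be stratified within the nine enrolment hospitals with a random block size of 6 or 9". Allocation is 1:1:1.

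**Endpoint.** The Primary outcome section defines success by a gain of at least 2 NRS points together with at least 6 points on the "Western Ontario and McMaster Universities Osteoarthritis Index (WOMAC) function score at week 8 compared with baseline". The function subscale is "scored from 0 to 68 with lower scores indicating better function". The Secondary outcomes section has both scores measured at week 0, so the baselines will be in hand.

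**Sample size.** The Sample size section assumes that "the success rates of the EA, MA and SA groups are expected to be 70%, 60% and 40%, respectively", tests at a two-sided 0.025, and gives 56 per group for EA versus SA, 128 for MA versus SA, and 160 after allowing for 20% loss.

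**Other models.** A generalised linear mixed-effect model is named as a sensitivity analysis in the per-protocol set. Its covariates are not stated.

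**The concern.** Two separate issues arise.

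**Hospital.** Blocking within hospitals makes the arms nearly equal in number at each site. Differences between hospitals therefore largely cancel out of the treatment difference. The pooled Z-test still counts them as error, because it takes the variance from the overall proportion. If hospitals differ in success rate, the standard error is too large and the true size falls below 0.025.

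**Baseline scores.** Success is a threshold on change, so the starting values may well help to predict it. These scores are not stratified. Their chance imbalance is real sampling variation, and the Z-test's standard error covers it correctly. The loss here is efficiency only: an adjusted analysis would remove some of that variation.

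What is at stake is precision for MA versus SA, the comparison that sets the trial's size. There is no bias and no inflated type I error.

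**Working it through.** **1. The plan's own figures.** Inputs from the Sample size section: p₀ = 0.40, p₁ = 0.60 (MA) or 0.70 (EA), two-sided α = 0.025 (z = 2.2414), power 80% (z = 0.8416).

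n = [2.2414·√(2p̄(1−p̄)) + 0.8416·√(p₁(1−p₁)+p₀(1−p₀))]² / (p₁−p₀)²

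- MA versus SA: (2.2414·√0.5 + 0.8416·√0.48)² / 0.04 = (1.5849 + 0.5831)² / 0.04 = 117.5, so 118. With continuity correction, (117.5/4)·[1 + √(1 + 4/(117.5·0.2))]² = 127.3, so **128**, as stated.
- EA versus SA: 51 without and 58 with the correction, against a stated 56.
- 128/0.8 = **160**, as stated.

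The plan was therefore sized for an unadjusted test.

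**2. Power of the planned Z-test, MA versus SA, 128 per arm, no correction.** Null SE = √(2·0.25/128) = 0.0625; alternative SE = √(0.48/128) = 0.0612. (0.20 − 2.2414·0.0625)/0.0612 = 0.978, giving **83.6%**. For EA versus SA at 128 per arm it is about 99.7%.

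**3. Why hospital inflates the standard error.** The overall variance splits as p(1−p) = mean within-hospital variance + between-hospital variance. The Z-test uses the total, while balance within hospitals leaves mainly the first part. The documents give no hospital effect, so the spread is assumed. At p = 0.40 the between-hospital share R² is 0.054 for a logit SD of 0.5 and 0.109 for 0.75.

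- SD 0.5: SE ratio 1/√(1−0.054) = 1.028; effective cut-off 2.2414·1.028 = 2.304; true size about 0.021.
- SD 0.75: SE ratio 1/√(1−0.109) = 1.059; cut-off 2.374; true size about 0.018.

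**4. Simulation for hospital.** Nine hospitals with 14 per arm each (126 per arm), overall group rates held at 40% and 60%:

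| Centre SD (logit, assumed) | Z-test size | Z-test power | Stratified CMH power | Gain (points) |
|---|---|---|---|---|
| 0 | nominal | 83.8% | 83.7% | none |
| 0.5 | 0.022 | 84.4% | 85.0% | 0.6 |
| 0.8 | 0.019 | 85.2% | 87.7% | 2.5 |

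Repeat runs gave Z-test sizes of 0.020 to 0.023 at SD 0.5 and 0.017 to 0.019 at SD 0.8.

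**5. Adding a baseline score.** 128 per arm, blocks of 6 or 9, 2,500 runs, MA versus SA; the slope is the assumed logit change per SD of baseline:

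| Centre SD | Slope | Z-test | CMH | Logistic (hospital + baseline) |
|---|---|---|---|---|
| 0 | 0 | 82.8% | 82.4% | 83.1% |
| 0 | 0.5 | 84.5% | 84.0% | 86.4% |
| 0.5 | 0.5 | 83.6% | 84.6% | 87.4% |
| 0.5 | 1.0 | 84.4% | 85.2% | 91.8% |

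Monte Carlo error is √(0.84·0.16/2500) ≈ 0.7 points. The logistic Wald test's size ranged from 0.022 to 0.035 across the scenarios run, against a Monte Carlo error of √(0.025·0.975/2500) ≈ 0.003. Part of its apparent gain may therefore be slight anti-conservatism.

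**The case against.** The other side has a good case, and most of it stands.

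- **The test is legitimate.** An unadjusted comparison of proportions is transparent, and any error from hospital runs against the trial's own hypothesis. This stands, and it is why the point is an improvement and not a defect that threatens the conclusions.
- **The sizes are assumed.** The documents give no hospital variation, no baseline WOMAC distribution and no correlation with success. A high baseline leaves more room to improve but could also mark less responsive disease. If neither factor is prognostic, there is nothing to gain. This stands.
- **A mixed model is already planned.** Its covariates may be set out in a document not shown. But it is a sensitivity analysis in the per-protocol set, so model and population change together. It does not replace adjustment in the primary comparison.

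Three stronger readings are tempting, but the documents do not support them.

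- *MA versus SA falls below 80% power.* Powers of 79.5% and 73.8% for the Z-test do appear if 40% and 60% are treated as rates in an average hospital. Adding hospital effects with SD 0.5 or 0.8 then shrinks the overall contrast to 59.5 − 40.5, about 18.9 points before rounding, or to 58.8 − 41.2 = 17.6 points. The Sample size section gives 40% and 60% as group rates, and holding them removes the shortfall.
- *The standard error is also wrong for the baseline scores.* They are not stratification factors, so it is valid for them.
- *Patients who cannot succeed distort the result.* Entry sets no minimum function score, and someone starting below 6 could not reach the threshold. Nothing shows that such patients would be more than rare.

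**Conclusion.** The point holds as a free efficiency gain, not as a shortfall. The primary test ignores the strata used in randomisation. If hospitals differ, it is mildly conservative: size about 0.022 to 0.019 against 0.025, with 0.6 to 2.5 points of power given up for MA versus SA at assumed centre SDs of 0.5 to 0.8.

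Adjusting for baseline as well could add a few points under moderate assumptions. The moderate case above (centre SD 0.5, slope 0.5) goes from 84.6% with CMH to 87.4%, subject to the caution about the logistic test's size. The hospital-only gain is the cleaner figure.

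The planned 80% is met by the Z-test in every scenario with the group rates held. EA versus SA, already near 99.7% at 128 per arm, has almost nothing to gain. The direction for hospital follows from the design; every magnitude rests on assumed effects.

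**What to change.** Before unblinding, and in the existing primary analysis set:

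- **Minimum:** compare EA with SA, and MA with SA, by a Cochran-Mantel-Haenszel test stratified by hospital.
- **Preferred:** fit a logistic model with treatment, hospital, baseline NRS and baseline WOMAC function. Report the standardised (marginal) risk difference for each comparison with its confidence interval.
- **Variance method:** name it in advance and confirm by simulation at about 14 patients per arm per hospital (128/9 ≈ 14.2) that it holds 0.025, since the plain Wald test ran somewhat high in some scenarios.
- **Supportive:** keep the unadjusted Z-test.

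The cost is a few sentences in the analysis section and a few lines of code. No patient, visit or measurement is added, and the sample size stays as it is. The choice should be fixed in advance, because adopting an adjusted analysis after seeing the results would not be credible.

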Electro-acupuncture (EA) and manual acupuncture (MA) are the most commonly used acupuncture styles in China. Therefore, we designed this multicentre randomised controlled trial to determine the effect of high-dose acupuncture (24 sessions in 8 weeks), compared with sham acupuncture (SA), in alleviating pain and improving function in patients with KOA.

The hypotheses are as follows.

In the first step (confirmatory test for EA versus SA):H0: Effect of EA = Effect of SAH1: Effect of EA ≠ Effect of SA

In the second step (confirmatory test for MA versus SA):H0: Effect of MA = Effect of SAH1: Effect of MA ≠ Effect of SA

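### The confirmatory hypotheses are numbered as steps but tested in parallel at 0.025, which leaves it unclear whether manual acupuncture can be claimed if electro-acupuncture fails; one Holm rule settles this and adds power

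*Protocol article*

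**What the plan says.** Three places in the protocol article bear on the confirmatory testing rule.

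- **Background, hypotheses.** One null and alternative pair appears under "In the first step (confirmatory test for EA versus SA", the other under "In the second step (confirmatory test for MA versus SA". Both alternatives are two-sided. No alpha is given, and nothing says that the second test depends on the result of the first.
- **Sample size.** "A two-sided significance level of 0.025 will avoid the inflation of type I errors". The trial is sized at that level for each comparison: "A sample size of 56 patients in each group is estimated to have 80% power" for EA versus SA, and "A sample size of 128 patients in each group is estimated to have 80% power" for MA versus SA. The larger figure is raised to 160 for 20% loss.
- **Statistical analysis.** The Z-test is to "compare the EA group and the SA group (and between the MA group and the SA group", with alpha set at "0.025 to adjust for the multiple comparison". The comparisons stand in parallel, with no order.

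**The concern.** Ordered confirmatory steps are the usual language of a fixed-sequence procedure, in which each hypothesis is tested at the full alpha and testing stops at the first failure. Splitting alpha equally is the Bonferroni procedure, which has no order. A fixed sequence needs no split, and a split needs no order. The article uses the vocabulary of one and the alpha of the other and does not connect them.

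The two procedures can give different answers for MA in two situations:

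- EA is not significant and MA has p at or below 0.025. The split claims MA; a fixed sequence would not.
- EA has p at or below 0.05 and MA has p between 0.025 and 0.05. A fixed sequence claims MA; the split does not.

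MA versus SA is one of the two confirmatory claims and the one that set the sample size. Its success criterion should be open to only one reading before the data are unblinded.

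**Working it through.** **Inputs (Sample size section).** "the success rates of the EA, MA and SA groups are expected to be 70%, 60% and 40%, respectively"; two-sided alpha 0.025 per comparison; power 80%; 20% loss.

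**1. Reproducing the stated sample size.** With critical values 2.2414 (two-sided 0.025) and 0.8416 (80% power), the pooled-variance formula is

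n = [2.2414 × √(2p̄(1−p̄)) + 0.8416 × √(p1(1−p1) + p2(1−p2))]² / (p1−p2)²

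and the continuity correction is n′ = (n/4) × [1 + √(1 + 4/(n|p1−p2|))]².

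- MA versus SA: n = (2.2414 × √0.50 + 0.8416 × √0.48)² / 0.04 = 117.5; corrected n′ = 127.3, so 128. This matches the article.
- EA versus SA: n = (2.2414 × √0.495 + 0.8416 × √0.45)² / 0.09 = 51.0; corrected n′ = 57.4, so 58. The article gives 56, which is close and does not drive the trial size.
- 128 / 0.8 = 160 per arm, as stated.

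The trial was therefore sized for the 0.025 split.

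**2. MA power under each rule.** The setting is 128 evaluable per arm, a shared sham arm and pooled Z-tests without continuity correction. Figures come from simulation of 1,000,000 trials and agree, to within about 0.001, with summing over the three binomial distributions. MA is claimed under:

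- *Split:* p(MA) ≤ 0.025.
- *Holm:* p(MA) ≤ 0.025, or p(EA) ≤ 0.025 and p(MA) ≤ 0.05.
- *Fixed sequence:* p(EA) ≤ 0.05 and p(MA) ≤ 0.05.
- *Order plus split:* p(EA) ≤ 0.025 and p(MA) ≤ 0.025.

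| True rates EA/MA/SA | Split | Holm | Fixed sequence at 0.05 | Order plus 0.025 |
|---|---|---|---|---|
| 70/60/40% (planned) | 0.849 | 0.900 | 0.900 | 0.848 |
| 60/60/40% (assumed here) | 0.849 | 0.886 | 0.834 | 0.757 |
| 40/60/40% (assumed here) | 0.849 | 0.851 | 0.037 | 0.018 |

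Only the first row uses the plan's own rates. The normal approximation for the first row agrees: (0.2 × √128 − 2.2414 × √0.50) / √0.48 = 0.978, a power of 83.6% at alpha 0.025. With 1.9600 in place of 2.2414 the value is 1.266, a power of 89.7% at alpha 0.05. EA power at 128 per arm exceeds 99%, so under the plan Holm nearly always tests MA at 0.05.

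**3. Type I error.** With all three rates at 40%, the chance of at least one false claim is about 0.048 for the split and 0.049 for a fixed sequence at 0.05. Holm makes a first rejection exactly when the split does, so its figure here is also 0.048.

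**4. Why Holm cannot lose against the present rule.** Its condition for MA contains the split's condition and adds a second route; the same holds for EA. Every claim available now stays available. The gain for MA at the planned rates is 0.900 − 0.849 = 0.051.

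**The case against.** The strongest reply is that the operative rule is already clear. The Sample size and Statistical analysis sections agree with each other and together form a complete Bonferroni procedure with valid error control. The step labels may be no more than list numbering, and a condensed article may leave further detail to a full protocol or analysis plan that is not shown here. Most of this stands, and it rules out several stronger readings.

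- *That the Background forbids an MA claim when EA fails.* A reader might infer this from the word step, but no such condition is written.
- *That multiplicity is penalised twice and MA falls below 80% power.* Nothing instructs anyone to apply order and split together. At the planned rates doing so would cost 0.1 point (84.8% against 84.9%). The figure of about 76% needs EA at 60%, which is an assumption made here and not in the plan. It is a sensitivity case only.
- *That power is wasted.* The stated 80% is met. The split also preserves the right to claim MA if EA fails, which a fixed sequence gives up: in the third row of the table its MA power is about 4%.

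What the reply does not remove is that the article itself supplies both the ordered hypotheses and the alpha rule and leaves them unconnected. This is a wording problem in what is stated, not a missing detail.

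**Conclusion.** The point holds as an unreconciled ambiguity with a cheap improvement attached. The step wording has no function beside the 0.025 split and leaves open whether MA can be claimed if EA fails. Neither the type I error nor the stated power is wrong.

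The improvement is worth about 5 percentage points of MA power, from about 85% to about 90%. That rests on the planned 70/60/40% rates, 128 evaluable patients per arm and an uncorrected pooled Z-test. The gain shrinks if EA works less well than planned (to about 4 points at 60/60/40%), but Holm never does worse than the present rule. The change should be made, though the trial remains valid without it.

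**What to change.** Remove the step labels from the hypotheses in the Background. In the Sample size and Statistical analysis sections, state one rule: Holm at an overall two-sided 0.05. The smaller of the two p-values is compared with 0.025; if it is significant, the other is compared with 0.05. Make the change before unblinding.

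The sample size of 160 per arm needs no revision, because the calculation at 0.025 remains a conservative basis. The cost is about one sentence in each of three places and no patients. The one drawback is that simultaneous confidence intervals matching Holm are less simple than Bonferroni intervals; 97.5% intervals can be reported alongside.

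If the sponsor prefers to keep the plain split, deleting the step labels alone would remove the ambiguity but forgo the power gain. A true fixed sequence at 0.05 per step is a trade-off and not a free improvement, since it gives up the MA claim whenever EA fails.

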## Discussion

KOA is one of the most common musculoskeletal diseases and causes considerable financial burden for society. This large trial will evaluate the efficacy of EA and MA versus SA in improving the symptoms of KOA.

This trial meets the methodological demand for adequate randomisation, allocation concealment, and blinding of patients, outcome assessors and statisticians. The ‘dose’ of acupuncture in our trial is intensive. It follows traditional Chinese medicine and is like clinical practice in China. There will be 3 treatment sessions per week in the 8-week treatment phase, giving a total of 24 sessions. The needles will be stimulated manually for at least 10 s at each acupoint and retained in situ for 30 min. Additionally, a suitable control group is critical for a well-designed clinical trial. It is accepted that acupuncture is effective for the treatment of KOA compared with a blank control [12]. However, whether acupuncture is better than SA is controversial. Thus, the control group will receive SA in this trial. Although a completely inert placebo control is not possible in acupuncture trials, superficial insertion at non-acupoints with no electric current is one of the most commonly used approaches for administering sham treatments in acupuncture trials, according to a literature review [34]. Patients who have received acupuncture treatment in the last 3 months and can distinguish SA from EA and MA will not be included. The same control has successfully been used to mask participants in other trials in China [24, 35]. Furthermore, all participants will be asked to guess which treatment they have received to test whether the participants are masked successfully. A further 2 × 2 factorial study might be designed to investigate use of acupoints versus non-acupoints, shallow acupuncture versus deep acupuncture, and their interaction.

Acupuncture alleviates pain by activating a variety of bioactive chemicals through peripheral, spinal and supraspinal mechanisms [36]. Opioids play a central role in acupuncture inhibition of all kinds of pain. Opioids desensitise peripheral nociceptors, decrease pro-inflammatory cytokines in peripheral sites and decrease cytokines in the spinal cord. A preclinical investigation indicated that adenosine mediates the effects of acupuncture [37]. EA of 2/100 Hz increased the release of both endomorphin-2 and dynorphin, whereas EA of (2 + 100) Hz increased the release of dynorphin but not of endomorphin-2 [38]. There is a more potent anti-nociceptive effect induced by 2/100 Hz EA, compared with that of (2 + 100) Hz EA. Thus, we chose 2/100 Hz.

A limitation is that this trial will not have enough power to test the difference between EA and MA. Second, the acupuncturists cannot be blinded due to the nature of the intervention. At the end of this trial, we hope the results will provide more reliable evidence and clarify the value of acupuncture as a treatment for KOA.

